## Follow-up of adverse events

All AEs will be followed until they have abated, or until a stable situation has been reached. Depending on the event, follow up may require additional tests or medical procedures as indicated, and/or referral to the general physician or a medical specialist.

SUSARs need to be reported till end of study within the Netherlands, as defined in the protocol.

# STATISTICAL ANALYSIS

Standard descriptive statistics will be used to summarize patient characteristics. Continuous data will be inspected for normality before analysis (Shapiro-Wilk), summarized with mean and standard deviation if normally distributed, or median and 25-75th centiles (Q1, Q3) if not normally distributed, and evaluated for differences with the One-Way ANOVA (if normally distributed) or Friedman Test (if not normally distributed). Categorical data will be summarized by frequency count and percentage calculations. Examination of possible associations between data will be done by Chi-Square Test or Logistic Regression. LA-type will be used as an interaction term to investigate the influence of the type of LA used. If needed, quantile regression, suitable for skewed data, will be used to identify confounders that may impact on postoperative quality of recovery scores. A two-tailed P-value <0.05 will be taken to indicate statistical significance.

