## Sample size calculation

Sample size was based on the primary outcome measure (QoR-15 score) and a superiority design. Following this design, an independent samples t-test was used, reasoning that one block would be superior to all others if it outperforms its best performing competitor. Based on previous research, a clinically relevant difference is determined at 6.0 points difference in QoR-15 scores.^27^ Also based on previous literature, a standard deviation of 10 is used.^28-30^ A power of 0.9 is used to minimize the chance of missing differences between the groups, as the differences in scores are likely to be small. In order to detect this difference between any of the three groups with a pre-defined p-value of 0.05, 180 patients are needed (distributed over three groups of 60). To account for 10% attrition, i.e. potential dropouts during the study process, a total of 198 patients will be included.

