# METHODS

## Study parameters/endpoints

### Main study parameter/endpoint

Score on the QoR-15 questionnaire.

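### A normality test on the trial data decides whether the primary QoR-15 result is a difference in means or a rank comparison with medians, so the effect measure is not fixed in advance or tied to the sizing

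*Protocol*

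**What the plan says.** Section 5.1.1 names the primary endpoint: "Score on the QoR-15 questionnaire". This is a continuous score.

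Section 7 then sets a general rule: "Continuous data will be inspected for normality before analysis (Shapiro-Wilk"). The outcome of that inspection switches two things:
- the summary: "summarized with mean and standard deviation if normally distributed, or median and 25-75th centiles (Q1, Q3) if not normally distributed";
- the test: "evaluated for differences with the One-Way ANOVA (if normally distributed) or Friedman Test (if not normally distributed").

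No other between-arm analysis of a continuous outcome is given, and QoR-15 is not exempted. Quantile regression appears only as a conditional tool for finding confounders.

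Section 3.4 sizes the trial differently: "an independent samples t-test was used", "a clinically relevant difference is determined at 6.0 points difference in QoR-15 scores" and "a standard deviation of 10 is used", with 90% power and 60 per group.

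**The concern.** A t-test with a standard deviation is a calculation about means. If the analysis keeps to means, the result can be read directly against the 6.0 points. If Shapiro-Wilk rejects, the plan moves to medians and a rank p-value. A difference in medians need not equal the difference in means, and a rank test's p-value estimates neither. Which of the two becomes the primary result depends partly on chance and partly on the shape of the scores, neither of which is known beforehand.

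At stake is whether the trial answers the question it was sized for, in a form that can be set against its own relevance threshold. The pre-test would be worth that price only if ANOVA were unreliable at this sample size, so that is what needs checking.

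**Working it through.** **Inputs from the protocol.** Difference 6.0, SD 10, power 0.9, 60 per group (section 3.4); two-sided 0.05 (section 7); three arms, 1:1:1 (section 5.2). The protocol gives no distributional shape for QoR-15, so every skew value below is an assumption.

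**Step 1: reproduce the sample size.** n per arm = 2(z₀.₉₇₅ + z₀.₉₀)²·SD²/δ² = 2 × (1.960 + 1.282)² × 100/36 ≈ 58.4, so 59. The exact t-test gives 59.35, so 60 per arm and 3 × 60 = 180. With the stated attrition allowance, 180 × 1.1 = 198. At 60 per arm the exact power for one pairwise comparison is 90.3%. The plan's figure is reproduced, and it rests on a mean difference.

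**Step 2: how often the gate switches the analysis.** With truly normal data and a separate test in each arm, the chance that at least one arm fails at 0.05 is 1 − 0.95³ = 14.3%. Simulation gives 13-14%. Applied once to the 180 pooled values, the rate is about 5%. At skew 0.5 the rates are 60% (any arm) and 53% (pooled); at skew 1.0 both are about 99%. Section 7 does not say whether the test is per arm, pooled or on residuals.

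**Step 3: whether ANOVA needs protecting.** Simulation with 3 × 60, SD 10 and shifted-gamma left skew; power is at arm means 0, 0, 6. The gated columns use ANOVA if all arms pass and Kruskal-Wallis otherwise. Size and power come from 4,000 trials per setting; the failure rates come from separate runs of 3,000-4,000.

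| Assumed left skew | At least one arm fails | Type I, ANOVA always | Type I, gated | Power, ANOVA always | Power, gated |
|---|---|---|---|---|---|
| 0 | 14% | 4.8% | 4.8% | 0.930 | 0.930 |
| 0.25 | 28% | 5.5% | 5.6% | 0.928 | 0.929 |
| 0.5 | 60% | 5.4% | 5.4% | 0.926 | 0.926 |
| 0.75 | 89% | 5.0% | 5.2% | 0.932 | 0.942 |
| 1.0 | 99% | 4.6% | 4.8% | 0.934 | 0.954 |

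The simulation standard error is √(0.05 × 0.95/4000) ≈ 0.3 points for size and √(0.93 × 0.07/4000) ≈ 0.4 points for power. A repeat run gave ANOVA size 4.3-5.4% and power 0.92-0.93. As a formula check, means 0, 0, 6 give f = √8/10 = 0.283 and an ANOVA power of 0.931. Power depends on the pattern of means: at 0, 3, 6 the same formula gives 0.839.

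ANOVA and Kruskal-Wallis disagree on significance in about 2-4% of trials.

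**Step 4: whether the two effect measures can differ.** If the arms have the same shape and differ only by a shift, the mean and median differences are equal. If shapes differ, they part:
- normal arm against an arm with left skew 1.0: mean difference 6.0, median difference about 7.7;
- assumed ceiling at 150 with latent means 140 and 146: mean difference about 4.5, median difference about 6.0;
- same ceiling with latent means 120 and 126: both about 6.0.

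In the second case, whether 6.0 points is reached depends on the branch taken.

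**The case against.** **The rule is pre-stated.** Both branches and the diagnostic are named, and a Shapiro-Wilk p-value is not chosen by looking at treatment effects. This stands. A reader might infer that the open-label design makes the switch open to manipulation, but lack of blinding does not change the result of a normality test, and the protocol gives no support for that reading.

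**The gate does no statistical damage.** This also stands if the fallback is a proper rank test for independent groups: the table shows size and power at least as good as ANOVA alone. Followed literally, the rule lowers power to about 0.86-0.87 at skew 0.5 or more. A reader might charge that loss to the gate, but it comes entirely from using Friedman, a test for related samples, on three independent arms. That is a separate matter.

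**Medians are in QoR-15 points too, and section 3.4 never says mean.** This partly stands. It would be too strong to say that a median result cannot be set against 6.0 points. But the t-test and SD make the sizing one of means, and the two differences coincide only under conditions the protocol does not establish.

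**The sentence is generic, and a SAP may fix the primary model.** The opening sentence of section 7 does concern patient characteristics. The rule that follows nevertheless covers the evaluation of differences in continuous data and is the only one offered. It is a stated rule, not a detail left open.

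**Conclusion.** The point holds as one of pre-specification and interpretation. The primary effect measure is left to a normality test on the trial data and may not be the mean difference on which the 60 per arm rests. With skew between 0 and 1.0 (assumed), the switch occurs in about 13% to 99% of trials when tested per arm. Over that range ANOVA holds its level near 5% and its power at 0.92-0.93 for means 0, 0, 6, so the gate guards against a problem that does not arise at this sample size.

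No inflation of type I error and no power loss from the gate itself has been shown, and the sample size is right for its own inputs. The failure rates depend on the assumed shape. The examples of diverging means and medians need unequal shapes or a ceiling, neither of which the protocol documents. The change is worth making because it is nearly free and brings section 7 into line with section 3.4.

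**What to change.** In section 7, exempt QoR-15 from the normality gate and name one primary analysis to be used whatever Shapiro-Wilk shows: one-way ANOVA or a linear model with arm, reporting pairwise mean differences with 95% confidence intervals. Robust or bootstrap standard errors can be specified if skew is a worry. Keep a rank test for independent groups (Kruskal-Wallis), with medians and quartiles, as a sensitivity analysis only.

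The cost is a few sentences, with no change to the sample size or data collection. The one statistical price is at strong skew: at about 1.0, ANOVA gives 0.934 against 0.954 for the gated procedure, so about 2 points of power are given up relative to a rank test.

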**Intervention (if applicable)**:

Participants will receive either FNB, FICB or PENG block.

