# STUDY DESIGN

This study will be a non-blinded, multicentre Randomized Controlled Trial (RCT), conducted in the ED of the MCL and other cooperating hospitals. Patients with a confirmed proximal- or neck of femur fracture are randomized to one of three treatment arms: FICB, FNB or PENG. After randomization regional anaesthesia is provided according to a standardized protocol and pain scores are measured at fixed time intervals. Patient reported outcomes are measured with a validated (QoR-15) questionnaire either 6-8 hours after block administration or before admittance to the operating room (OR), whichever one comes first. A flowchart of the study design can be found below (*Figure 1*).

**Figure 1**. Flowchart of the study design.

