## Randomisation, blinding and treatment allocation

Block-randomization will be performed via the REDCap randomization module on a 1:1:1 basis for every participating centre.

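### The Friedman test named for non-normal data needs related samples; the three arms are independent, so it does not apply and Kruskal-Wallis should replace it

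*Protocol*

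**What the plan says.** Protocol section 7 (Statistical Analysis) sets a two-step rule. "Continuous data will be inspected for normality before analysis (Shapiro-Wilk"), and the data are then "evaluated for differences with the One-Way ANOVA (if normally distributed) or Friedman Test (if not normally distributed"). The significance rule is "A two-tailed P-value <0.05 will be taken to indicate statistical significance".

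The primary endpoint in section 5.1.1 is "Score on the QoR-15 questionnaire". Section 7 gives it no separate between-arm test. The secondary endpoints in section 5.1.2 include pain scores and rescue opioid in mg/hour, which are also continuous.

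The design is parallel-group. In section 2, patients "are randomized to one of three treatment arms: FICB, FNB or PENG". The Summary says "Participants will receive either FNB, FICB or PENG block". Section 5.2 allocates "on a 1:1:1 basis for every participating centre", with no matching of patients across arms. For the sample size in section 3.4, "an independent samples t-test was used".

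**The concern.** The Friedman test ranks values within blocks. Each block, whether a patient measured under every condition or a matched set, must supply exactly one value per treatment. One-way ANOVA, which section 7 offers as its counterpart for normal data, is for independent groups. The two are therefore not alternatives for the same data layout, and only the ANOVA fits this trial.

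If the QoR-15 score fails the normality check, the protocol directs the analyst to a test for which the data have no structure. The analyst must then either depart from the protocol on the primary endpoint after seeing the data, or drop patients to equalise the arms and line up unrelated patients in arbitrary rows. The same applies to pain scores and opioid use.

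**Working it through.** **1. The plan's own sample size.** Inputs from section 3.4: difference 6.0, SD 10, power 0.90, alpha 0.05, which section 7 makes two-sided.

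- Normal approximation: n = 2(1.960 + 1.282)² × 10² / 6² = 58.4, so 59 per arm.
- Independent-samples t-test (noncentral t): n = 59.35, so 60 per arm and 180 in total. Power at 60 per arm is 0.903.
- Enrolment: 180 × 1.10 = 198.

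The stated 180 and 198 reproduce, on a calculation that treats the arms as independent.

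**2. Does the design supply blocks?**

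- Patient as block: no. Each patient receives one block type and has one planned QoR-15 measurement.
- Matched sets: none. Randomisation is 1:1:1 within centre, without matching.
- Centre as block: no. Friedman takes one value per cell, and a centre contributes several patients per arm.

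**3. What happens if the test is run anyway?** With k = 3 arms, n rows and N = 3n:

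- Friedman: Q = 12 / (nk(k+1)) × ΣRⱼ² − 3n(k+1), with ranks taken within rows.
- Kruskal-Wallis: H = 12 / (N(N+1)) × Σ(Rⱼ²/n) − 3(N+1), with ranks taken over all patients.

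Q requires the same n in each arm. With arms of 60, 58 and 61 the routine stops with an error. Since section 3.4 allows for 10% attrition, unequal arms are likely.

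With equal arms, the rows must be invented, and Q changes with them. In one simulated dataset (60 per arm, Kruskal-Wallis p = 0.0014), 3,000 random regroupings gave a Friedman p-value with a 95% range of 0.0002 to 0.074 and a maximum of 0.28. This illustrates the dependence on grouping; the range itself will differ between datasets.

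**4. Power in the setting that triggers the test.** The protocol gives no distribution, so this rests on an assumption: reflected gamma(2) errors (left-skewed), SD 10, 60 per arm, 20,000 trials per row, Friedman on arbitrary triplets.

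| Arm means | ANOVA | Kruskal-Wallis | Friedman |
|---|---|---|---|
| 0/0/0 (type I error) | 0.049 | 0.050 | 0.049 |
| 0/0/6 | 0.924 | 0.976 | 0.928 |
| 0/3/6 | 0.838 | 0.942 | 0.857 |

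Friedman against Kruskal-Wallis: 0.976 − 0.928 = 0.048, and 0.942 − 0.857 = 0.085. Smaller repeat runs gave 0.92 against 0.98 for 0/0/6, and between 0.85 against 0.93 and 0.86 against 0.95 for 0/3/6. The loss is therefore about 5 to 9 percentage points.

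**5. How likely is the trigger?** With simulated left-skewed data and Shapiro-Wilk applied to all 180 values, normality is rejected in 67% of trials at skewness 0.5, 94% at 0.7 and over 99% at 1.0. If each arm is tested separately, at least one rejects in 58%, 84% and 98%.

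**The case against.** Several points on the other side have force.

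- **The rule is general.** The sentence speaks of continuous data and does not name the QoR-15. Applying it to the primary endpoint is an inference. It is a reasonable one, because the protocol gives no other between-arm test for that score. The quantile regression in section 7 is optional and meant for finding confounders, so it does not replace the test.
- **Friedman might be meant for repeated pain scores.** It could test change over time within a patient. But section 7 pairs it with one-way ANOVA for all continuous data, and the objectives compare blocks, not time points.
- **The mistake would probably be noticed.** With unequal arms the software fails, and a competent analyst would switch to Kruskal-Wallis. That is likely, but it would be an unplanned change made after seeing the data.

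A reader might also infer three stronger claims that the documents do not support.

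- **That the test inflates false positives.** It does not. On arbitrary triplets type I error stays near 5%. The accurate word is inapplicable.
- **That about ten points of power are lost.** With normal errors and means 0/0/6, Kruskal-Wallis has power 0.914 and Friedman 0.816. But with normal data the plan mostly uses ANOVA. Following the rule as written, Friedman is triggered in about 5% of such trials (pooled check) to 14% (any arm), and the power of the whole rule is 0.91 to 0.92.
- **That the normality check should give way to a fixed mean-based primary analysis.** This is a separate trade-off. The two-stage rule held type I error at 4.7 to 5.0% in simulation, and in the skewed setting ANOVA (0.924 and 0.838) does no better than Friedman (0.928 and 0.857), so it would not recover the lost power.

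**Conclusion.** The point holds as a clear error in stated text: a related-samples test is prescribed for three independent arms, against the protocol's own design and sample-size method. Nothing elsewhere in the protocol corrects it. Since the wrong test is written down, this is not a detail merely left to a statistical analysis plan.

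The case for correction rests on the test not fitting the design. It cannot be computed with unequal arms, and with equal arms its p-value depends on a grouping that the analyst would have to invent. The power loss of about 5 to 9 points is secondary. It arises only if Shapiro-Wilk rejects normality and triplets are then forced, and its size depends on the assumed gamma(2) shape and arm-mean patterns, neither of which the protocol gives. Rejection is plausible for a bounded patient-reported score and for opioid use, so this branch of the rule is a realistic path to the primary result.

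**What to change.** In protocol section 7, name the Kruskal-Wallis test in place of the Friedman test for between-arm comparisons of non-normal continuous data, with the Mann-Whitney test for pairwise comparisons. The rest of the normality rule can stand as far as this point goes.

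The cost is one edited sentence, notified as an amendment under section 9.2. Data collection does not change, and the sample size stays at 180 evaluable and 198 enrolled.

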**Secondary Objective(s):**

- To compare pre-operative pain scores 15 min, 30 min, and 1 hour post-block placement in patients receiving PENG, FICB and FNB in the ED.
- To compare the amount of rescue medication, calculated as mg/hour given IV in the ED after block placement or SC/IO in the ward during the first 12 hours after block placement or until operation.
- To compare complications of block placement in patients receiving PENG, FICB and FNB in the ED in the first 24 hours after block placement.

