### Secondary study parameters/endpoints (if applicable)

- - Pre-operative pain scores at 15 min-, 30 min-, and 1 hour post-block placement.
  - The amount of rescue medication calculated as mg/hour given IV in the ED after block placement or SC/IO in the ward during the first 12 hours after block placement or until operation.
  - Number and type of adverse and serious adverse events.

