## Study procedures

Before the start of the data collection, a refamiliarization session for all three nerve block procedures will be hosted in each individual center. In this refamiliarization session, an expert in POCUS will provide theoretical and practical training in block placement for each of the three blocks, and will test and log the skill level of the participating physicians in a dedicated training log. Only physicians who are able to perform all three blocks in line with the NYSORA guidelines are eligible for participation in the study.^31-33^

[figure not shown]

**Figure 2**. Timeline of the study procedure, showing which data will be collected at what time point.

Data will be gathered at 6 different time points (T1-T6). *Figure 2* shows a detailed timeline of data collection.

Pre-block characteristics (demographic data (age, sex, weight), ASA score, pain scores (VAS) during rest and light elevation of the affected leg, type of fracture, analgesics administered before hospital admission (including medication routinely used by the patient), block characteristics (type of block, visualization of landmarks, amount- and type of LA administered, timing of block placement), and post-block characteristics (total amount of opioids administered in the first 12 hours after block administration and (S)AE’s) will be reported in an electronic case report form (appendix IV).

The primary endpoint, quality of recovery, will be measured either 6-8 hours post-block, or pre-OR (whichever one comes first) with the Quality of recovery-15 (QoR) patient-reported outcome questionnaire that measures the quality of recovery after surgery and anaesthesia.^34^ To ensure patients will be adequately rested for their operation, QoR-15 registration will be postponed until the next morning for blocks placed between 17.00 and 22.00 hours, as QoR-15 registration would then fall between 23.00 and 6.00. The QoR-15 questionnaire can be found in the appendices (*Appendix III*). Previous studies have shown a good convergent validity between the QoR-15 and the visual analog scale (VAS). Additionally, validity of the QoR-15 is supported by a negative correlation with duration of surgery and duration of hospital stay, and the QoR-15 shows excellent internal consistency, split-half reliability, test–retest reliability, and responsiveness.^34^

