**Pijnscores lichte elevatie been (VAS)**

[figure not shown]
15 min na block :

[figure not shown]
30 min na block :

[figure not shown]
1 uur na block :

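### Section 7 compares post-block pain between arms without using the pre-block VAS, so the comparison at each time point is valid but less precise than the data allow

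*Protocol*

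**What the plan says.** The first secondary objective in section 1 is set by time point: "To compare pre-operative pain scores 15 min, 30 min, and 1 hour post-block placement in patients receiving PENG, FICB and FNB in the ED". Section 5.1.2 lists the matching endpoint: "Pre-operative pain scores at 15 min-, 30 min-, and 1 hour post-block placement".

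Appendix IV has one set of three post-block readings at rest and another on leg elevation, headed "Pijnscores lichte elevatie been (VAS". Section 5.3 places among the pre-block characteristics "pain scores (VAS) during rest and light elevation of the affected leg". Each patient therefore has a baseline in both conditions and six post-block readings.

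Section 7 gives one rule for all continuous data, chosen by a normality check. Data are "evaluated for differences with the One-Way ANOVA (if normally distributed", "or Friedman Test (if not normally distributed". Neither test takes a covariate. The only regression that section 7 names for a continuous outcome concerns quality-of-recovery scores, not pain: "If needed, quantile regression, suitable for skewed data, will be used to identify confounders".

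**The concern.** Post-block pain plausibly depends in part on how much pain the patient had before the block. A one-way ANOVA leaves that between-patient variation in the error term. If the pre-block VAS predicts the later readings, the arm differences at 15, 30 and 60 min get wider confidence intervals and lower power than the collected data support. The ANOVA also does nothing about chance differences between the arms in pre-block pain.

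At stake is precision on the first-listed secondary objective. The ANOVA's validity at each time point is not in doubt, and the primary QoR-15 analysis is unaffected.

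**Working it through.** **Inputs from the protocol.** 60 evaluable patients per arm (section 3.4). Three arms, 1:1:1 (section 5.2). Post-block readings at 15, 30 and 60 min (section 5.1.2). Pre-block VAS in both conditions (section 5.3). Significance rule (section 7): "A two-tailed P-value <0.05 will be taken to indicate statistical significance".

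**Assumptions, not in the protocol.** VAS SD 25 mm; one block better than the other two by 12 mm; correlation r between pre- and post-block VAS of 0.3 to 0.5; correlation ρ between post-block readings of 0.5 to 0.9, as given at each step.

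**1. The plan's own figure.** Section 3.4 uses a t-test with difference 6.0, SD 10, power 0.9 and two-sided 0.05. This needs 59.35, so 60 per arm (power 0.903 at 60). The figure reproduces. It concerns QoR-15 and is used here only for the group size; the protocol states no power for pain.

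**2. Unadjusted ANOVA at one time point.** With means 0, 0 and 12 the overall mean is 4, and the squared deviations sum to 16 + 16 + 64 = 96. The noncentrality is 60 × 96 / 25² = 9.216 on 2 and 177 degrees of freedom, so power is 77%. The SE of a pairwise difference is 25 × √(2/60) = 4.56 mm.

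**3. Adjusted for pre-block VAS at the same time point.** The residual variance is multiplied by 1 − r², the noncentrality is divided by it, and one degree of freedom is lost.

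| r | Variance ratio 1 − r² | SE (mm) | Noncentrality | Power |
|---|---|---|---|---|
| none | 1 | 4.56 | 9.22 | 77% |
| 0.3 | 0.91 | 4.35 | 10.13 | 81% |
| 0.4 | 0.84 | 4.18 | 10.97 | 85% |
| 0.5 | 0.75 | 3.95 | 12.29 | 89% |

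The SE falls by 5% (√0.91 = 0.954) to 13% (√0.75 = 0.866). To match this without adjustment would take 60/0.91 ≈ 66 to 60/0.75 = 80 patients per arm. At r = 0 there is no gain.

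**4. Does modelling the three readings together add precision at each time point?** With complete data and no baseline term, a repeated-measures model with unstructured covariance and arm-by-time gave the same estimates as three separate ANOVAs on one simulated data set, and the same SEs: 3.573, 3.246 and 3.495 under both. With the baseline included, per-time ANCOVA and the mixed model gave SEs of 4.370 and 4.364 (ρ = 0.5, r = 0.3), and 3.964 and 3.961 (ρ = 0.7, r = 0.5). These differences are under 0.2%.

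**5. Missing last readings.** If a fraction m of last readings is missing and the preceding reading is used, the variance ratio is 1 − mρ². For m = 5% and ρ = 0.5 this is 1 − 0.05 × 0.25 = 0.9875. For m = 10% and ρ = 0.9 it is 1 − 0.10 × 0.81 = 0.919. The gain is about 1–8% of variance; both m and ρ are assumed.

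**6. A first-hour average instead.** Its variance relative to one reading is (1 + 2ρ)/3, which is 0.67 to 0.87 for ρ = 0.5 to 0.8. If the 12 mm difference holds at all three readings, power is 92% to 83%. If it holds at one reading only, the average difference is 12/3 = 4 mm and power is 15–18% (19–21% with baseline), against 77% for the ANOVA at that reading.

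**The case against.** **The model for a secondary endpoint belongs in the SAP.** The SAP is not shown and may refine section 7. But the protocol is not silent here: it names the tests for continuous data, and neither uses the baseline. The objection lowers the weight of the point without removing it.

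**The ANOVA is valid and answers the stated question.** This stands. The objective is set by time point, and a one-way ANOVA at each time compares the arms without bias. The point is one of efficiency.

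**The gain rests on assumed figures.** This also stands. The protocol gives no SD, difference or correlation for pain. The correlation could be low if the blocks work well, and the exclusion of patients with a pre-block score below 2 out of 10 narrows the baseline range. Against that, one covariate costs one degree of freedom out of 177.

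**A reader might infer more than the protocol supports:**

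- *Section 7 offers nothing but a one-way ANOVA.* It does not: the same sentence names the Friedman test. That test is for related samples and does not suit three parallel arms, but that is a separate matter from the unused baseline.
- *Separate tests waste the within-patient information, so a repeated-measures model must be more precise at no cost.* For the time-specific comparisons the protocol asks for, step 4 shows no such gain with complete data. The model also brings a covariance structure and a missing-at-random assumption.
- *The first-hour average should be the main result.* The protocol names no such target, and step 6 shows that an average would dilute a difference confined to one reading, such as faster onset.

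**Conclusion.** The point holds as a recommended improvement in precision on a secondary objective. The pain analysis in section 7 is valid at each time point but leaves a collected and plausibly prognostic baseline unused.

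For a baseline correlation of 0.3 to 0.5, the variance of each time-specific difference falls by 9% to 25%. Under the 12 mm and 25 mm assumptions, power moves from about 77% to 81–89%. All of these inputs except the 60 per arm are assumptions, and the gain shrinks to nothing as the correlation approaches zero.

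The protocol does not support calling the ANOVA invalid, nor the claim that a repeated-measures model is needed to recover lost precision. Almost all of the per-time gain comes from the baseline term. What the mixed model adds is the use of incomplete readings, worth about 1–8% of variance if 5–10% of last readings are missing.

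**What to change.** In section 7, give pain its own sentence in place of the general rule. Analyse VAS at 15, 30 and 60 min, separately for rest and for leg elevation, adjusted for the pre-block VAS of the same condition. Either form is acceptable:

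- ANCOVA at each time point, with arm and pre-block VAS; or
- one linear mixed model with arm, time, arm-by-time, pre-block VAS and its interaction with time.

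Report the three time-specific arm differences with 95% CI as the result for this objective. A first-hour average may be given as supplementary only.

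Section 5.3 already provides for the baseline, so no new data or patients are needed. It is worth confirming that the eCRF holds the pre-block VAS for both conditions: the legible VAS labels in Appendix IV are for 15, 30 and 60 min only, and its graphics could not be read. The cost is a change of wording and a slightly more complex model to report, plus a missing-at-random assumption if the mixed model is chosen.
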